#### Postwear Surveys

Participants will complete a postwear survey on their experience of wearing the Skyn at their last meeting. This survey was adapted from Alessi et al [29]. If they were randomized to the CM group, they would also complete a survey on their CM experience. This study was adapted from Miguel et al [49].

#### Feasibility

Feasibility is defined by enrolment, participation, device tampering, removals, adjustments, malfunction rates, and the number of TAS returned (Textbox 1).

Feasibility outcome definitions.
**Enrolment**
Recruitment rate, willingness of participants to enroll, and willingness of clinicians or services to recruit participants.
**Participation**
Enrolled participants who attended meetings or intervention, follow-up rate, response rate, compliance, reasons for incomplete participant data (meeting nonattendance, data overwritten, and technical fault).
**Tampering**
Tampering with the transdermal alcohol sensor (TAS) to hide alcohol consumption or to stop its recording.
**Removals**
Removal (more than 2 minutes where the temperature was <30 °C).
**Malfunction**
Device error, missing data due to technical fault, charging issues, and syncing issues.
**TAS return**
Number of TAS successfully returned intact.

### Sample Size

The target is to recruit 30 participants within 6 months. This sample size was influenced by budget and time constraints and the number of participants considered suitable for meeting and carrying out the study’s aims of feasibility, as recommended for pilot studies by Lancaster et al and Browne [50-53].

### Randomization

This is a nonblinded study. Participants will be individually randomized into either the control group or the CM group (1:1 ratio). The randomization will be remote and overseen by an independent statistician using a sealed envelope randomization technique. The statistician (an independent researcher not involved in the study) generated a random list with Stata, with each allocation on a piece of A4 paper printed and sealed in the appropriate envelope (numbered 1-30). When a participant is enrolled, the researcher will then open the corresponding envelope to the participant's study ID for group allocation. Therefore, no member of the research team is aware of the group allocation until a participant enrolls on their first research visit.

### Recruitment

To achieve adequate participant enrollment and reach the target sample size, we plan to have regular communication with each participating service. We will attend each service regularly to inform staff of the ongoing recruitment and attend service user groups to discuss the research with eligible individuals.

### Statistical Analysis

Baseline and demographic variables will have descriptive statistics reported. Outcome measures will be conducted by intervention groups (control and CM) and then compared between the groups.

We will report on the feasibility measures stated earlier. Descriptive data from the postwear survey will be reported, and statistical comparisons of the postwear survey responses between groups will be performed using 2-tailed *t* tests. In instances where the data are ordinal or the assumptions of the paired samples *t* test are not met, the nonparametric alternative to the paired samples *t* test will be used, the Mann-Whitney *U* test. Given the small sample size and nature of this pilot study, the primary purpose of these results will be to inform the potential barriers and limitations and challenges faced in implementing CM for future work.

To assess TAS accuracy, the TAC data will be compared against the TLFB to address the secondary outcomes of accuracy. The analysis will focus on the sensitivity, specificity, positive predictive value, and negative predictive value of TAC compared to TLFB as the gold standard. Sensitivity in detecting alcohol events and specificity in classifying an alcohol-drinking day versus a nonalcohol-drinking day will be assessed. Recorded drinking and abstinent days will be analyzed using Spearman Rank correlations comparing different alcohol-drinking day TAC criteria. All statistical analyses will be conducted using SPSS (version 28; IBM Corp).

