**Methods:**

The target sample size is 30 (15 randomized to each group). Participants will be recruited through poster adverts at alcohol services. Both groups (control and CM) will wear the TAS (BACtrack Skyn) for 2 weeks in the context of their usual treatment, meeting with the researcher every other weekday. In the last meeting, the participants will complete a postwear survey on their experience of wearing the TAS. The CM group will also receive small financial incentives for low or no alcohol consumption, as measured by the TAS. On days where the TAC peak is below a set threshold (<115.660 g/L), CM group participants will be rewarded with a £5 (US $6.38) voucher. There are financial bonuses if this target is achieved on consecutive days. The researcher will monitor TAC for each day of the study at each research visit and allocate financial incentives to participants according to a set reinforcement schedule.

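### The rule for choosing the postwear survey test refers to the paired-samples t test, although the two groups are independent and no pairs exist

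*Protocol article*

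**What the plan says.** Under Statistical Analysis, the protocol article states that "statistical comparisons of the postwear survey responses between groups will be performed using 2-tailed" t tests. That sentence does not say whether the t test is paired or independent.

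The next sentence gives the rule for leaving the t test. It opens "In instances where the data are ordinal or the assumptions of the paired samples" t test are not met. It describes the replacement as "the nonparametric alternative to the paired samples" t test and then names it: "test will be used, the Mann-Whitney" U test. The paired test therefore appears twice, once as the test whose assumptions are checked and once as the test that the fallback replaces.

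The design is described elsewhere. Randomization says: "Participants will be individually randomized into either the control group or the CM group (1:1 ratio"). Postwear Surveys says: "Participants will complete a postwear survey on their experience of wearing the Skyn at their last meeting". The Methods paragraph of the abstract says: "The target sample size is 30 (15 randomized to each group").

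**The concern.** A paired-samples t test works on the difference within each pair, and its main assumption is that those differences are roughly normal. It needs either two measurements on one person or persons matched across groups. This trial has neither for the survey, so the quantity to be checked before choosing the test is undefined.

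The fallback also belongs to a different design. Mann-Whitney U compares two independent samples. The rank-based counterpart of the paired t test is the Wilcoxon signed-rank test.

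An analyst who took the wording literally would have to match control and CM participants by their position in the file. The p-value would then depend on how the file was sorted, and with unequal numbers of responders the surplus in the larger arm would be left out. The article reports that analysis was already under way, so the wording could bear on results about to be reported.

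**Working it through.** The article gives no alpha, effect size, standard deviation or power for this comparison, so there is no planned figure to reproduce. The check has two parts.

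**1. Test against design**

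| Feature | Protocol article | What a paired test needs |
|---|---|---|
| Comparison | Control v CM (Statistical Analysis) | Two linked values per unit |
| Allocation | Individual, 1:1, no matching described (Randomization) | Matched pairs, or |
| Survey timing | Once, at the last meeting (Postwear Surveys) | Repeated measurement of one person |
| Fallback | Mann-Whitney U (Statistical Analysis) | Wilcoxon signed-rank |

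Neither route to a pair exists. The comparison and the fallback both fit independent groups. Only the two mentions of the paired test do not.

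**2. What would follow if a paired test were run**

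Inputs: 15 per arm (abstract, Methods). Two-sided alpha of 0.05 and the standardised differences below are assumptions.

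*Degrees of freedom and critical values*
- Independent samples: 15 + 15 − 2 = 28, critical t = 2.048.
- Paired on 15 arbitrary pairs: 15 − 1 = 14, critical t = 2.145.

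*Power.* With arbitrary pairing the two values in a pair are independent, so each difference has variance 2σ². The noncentrality is therefore the same for both tests, d / √(2/15), and only the degrees of freedom differ.

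| Assumed d | Noncentrality | Independent, 28 df | Arbitrary pairs, 14 df | Loss (points) |
|---|---|---|---|---|
| 0.5 | 1.37 | 26.2% | 24.8% | 1.5 |
| 0.8 | 2.19 | 56.2% | 53.2% | 3.0 |
| 1.0 | 2.74 | 75.3% | 72.2% | 3.1 |

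(Losses are taken from unrounded values.)

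*Type I error.* In 100,000 simulated null comparisons of 15 v 15, the two-sided 0.05 rejection rate was 4.9% with arbitrary pairing and 4.9% with the independent test for normal data. For uniform five-point items it was 5.2% and 5.2%.

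*Dependence on row order.* In one simulated data set of 15 v 15 (normal, true difference 0.7 SD), the independent t test gave p = 0.231. Shuffling one arm 5,000 times and running the paired test gave p from 0.033 to 0.360, with a central 95% of 0.114 to 0.324. This illustrates that the answer is not unique. It does not predict the trial's result.

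*Unequal numbers.* With 15 v 14 responders the paired calculation has no partner for one person. It fails unless that person is removed.

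**The case against.** The strongest reply is that this is a wrong label on a sound plan. The sentence that sets the analysis says only two-tailed t tests between groups, and Mann-Whitney U is right for independent groups. Ordinal items go straight to Mann-Whitney U whatever the t test is called. Together these suggest that an independent-samples analysis was meant. The comparison also serves a secondary objective, acceptability, and the article says that these results are mainly to inform barriers and challenges for future work. The feasibility outcomes and the accuracy analysis do not use it.

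Most of this stands, and it limits the weight of the point. It does not remove the contradiction. The paired test is the only t test whose type is given, it is named twice, and the rule for changing test rests on its assumptions.

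Three stronger readings are tempting, and the documents do not support them:
- *A paired t test is the planned analysis.* The operative sentence leaves the type open, and the paired wording appears only in the assumption check and the description of the fallback.
- *The paired test cannot be run.* With equal numbers of responders, software returns a result if the arms are set out as two columns. The result is arbitrary, but it exists.
- *The error would produce false positives.* Arbitrary pairing keeps the nominal error rate, as shown above. The harm is a p-value that depends on sorting, discarded responders and slightly lower power.

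**Conclusion.** The point holds as an internal contradiction in the Statistical Analysis section. The rule for choosing the survey test relies on the assumptions of a test that does not fit two independent groups surveyed once, and it pairs that test with the wrong nonparametric counterpart.

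Its size is modest. Even if a paired test were run, the cost at 15 per arm would be 14 degrees of freedom and roughly 1.5 to 3 points of power, plus any surplus responders in the larger arm, with no inflation of type I error. These figures assume a two-sided alpha of 0.05, standardised differences of 0.5 to 1.0, and a row order unrelated to the responses. The article gives neither the survey item scales nor the number of responders per arm. If most items are ordinal the wording affects little, and if most are treated as continuous it affects more. No sample size rests on this comparison: under Sample Size the target is attributed to budget, time and recommendations for pilot studies.

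**What to change.** In the fallback sentence of Statistical Analysis, replace paired samples with independent samples in both places. State that the t test assumptions are checked within each arm. Keep Mann-Whitney U for ordinal items and for cases where those assumptions fail, so that the t test, its assumption check and its fallback all refer to the same design.

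It would also help to say in the preceding sentence that the two-tailed t tests are independent-samples tests. Welch's version and a 95% confidence interval for the between-arm difference are optional additions and are not needed to cure the contradiction.

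The cost is an edit to one or two sentences. No data collection, sample size or other analysis changes. If any survey comparison has already been run as a paired test, it should be rerun as an independent-samples comparison before reporting.

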### Measures

#### BACtrack Skyn

The TAS that will be used is the BACtrack Skyn. It will be worn on the participant’s preferred wrist, but they will be allowed to change which wrist they wear it on during the study period. The Skyn will continuously measure the TAC while being worn, as well as skin temperature (Celsius). Output will be viewed at 1-minute intervals. The participants can remove the TAS at any time if they do not wish to wear it and will be required to remove it for bathing as it is not waterproof. The CM group will be told they can remove it once a day for up to 60 consecutive minutes to bathe and still be eligible for their CM reward. If removed for longer than an hour, then they will no longer be able to receive the CM reward, even if the other data suggest no alcohol consumption. If they wear the TAS according to this and the TAC does not increase above our set threshold of 115.660, they will be eligible for the CM reward for that day. We will explore various TAC criteria when defining a drinking event: TAS 15 (TAC>15, >15 minutes), TAS 60 (TAC>15, >60 minutes), and TAS 90 (TAC>15, >90 minutes).

To note, an alcohol drinking day defined by TAC is different from the CM intervention criteria, which allows for a low amount of drinking and has a higher TAC criterion. There are 2 distinctions: those in the CM group at each meeting will have their data examined for meeting the CM rewards criteria, and then in the analysis at the end after all data collection, all participants will have an accuracy analysis conducted where participant days will be defined as alcohol-drinking days (according to TAC/minute criteria) or nonalcohol drinking days.

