#### TLFB

A TLFB will be completed at meetings 2-7 to assess self-reported alcohol consumption and compare it against the TAC data. The TLFB is a calendar-based measure to record self-reported substance use. Each date of the study period was completed at the following meeting. Any reported alcohol consumption on the TLFB will define that day as an alcohol-drinking day. Days will be recorded as 12 AM to 11:59 PM.

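### Spearman correlation does not measure how well each TAC drinking-day criterion agrees with TLFB, and sensitivity is worded per event where only days are available

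*Protocol article*

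**What the plan says.** The Statistical Analysis section of the protocol article sets out the accuracy analysis in three steps. The main step is: "The analysis will focus on the sensitivity, specificity, positive predictive value, and negative predictive value of TAC compared to TLFB as the gold standard". Next comes the unit: "Sensitivity in detecting alcohol events and specificity in classifying an alcohol-drinking day versus a nonalcohol-drinking day will be assessed". Last comes the comparison of criteria: "Recorded drinking and abstinent days will be analyzed using Spearman Rank correlations comparing different alcohol-drinking day TAC criteria".

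The criteria are introduced under BACtrack Skyn: "We will explore various TAC criteria when defining a drinking event: TAS 15 (TAC>15, >15 minutes", followed by TAS 60 and TAS 90, which use the same TAC cut-off for more than 60 and more than 90 minutes. The same section then puts the accuracy analysis on days: "all participants will have an accuracy analysis conducted where participant days will be defined as alcohol-drinking days (according to TAC/minute criteria) or nonalcohol drinking days".

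The reference is defined under TLFB: "Any reported alcohol consumption on the TLFB will define that day as an alcohol-drinking day. Days will be recorded as 12 AM to 11:59 PM".

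The article does not say whether Spearman is applied to yes/no days or to one count per participant. I read it as relating the days flagged by each criterion to the days reported on TLFB. It plans no confidence interval, standard error or test for the four accuracy indices.

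**The concern.** TAS 15, 60 and 90 are nested: a day that meets the 90-minute rule also meets the 60- and 15-minute rules. By construction they differ in how many days they flag, that is, in systematic over- or under-calling. On counts, rank correlation ignores that kind of error, so a high rho says little about which criterion agrees with TLFB.

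On yes/no days, Spearman changes with the share of drinking days. The section says outcome measures are produced by group and then compared, and CM is meant to reduce drinking. The two arms could therefore show different correlations with an identical sensor.

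The unit is a separate problem. If sensitivity is counted per event, TLFB as defined supplies no event to count against, and sensitivity would not come from the same 2×2 table as day-level specificity.

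At stake are the reported TAS accuracy, which is a named secondary objective, and any view on which TAC criterion a later trial should use. The Discussion already cites a high correlation with self-report in the team's previous work as promising, so a high rho here could be over-read.

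**Working it through.** **Inputs.** From the article: 30 planned participants (Sample Size: "The target is to recruit 30 participants within 6 months"), two weeks of wear (about 14 days each), three criteria, and TLFB as a daily yes/no. The target of 30 has no formula behind it and no accuracy figure is stated, so there is no plan figure to reproduce. Drinking prevalence, sensor performance and intraclass correlation (ICC) are not in the article. The values below are assumptions.

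**1. Spearman on per-participant counts.** Take 30 participants whose TLFB counts t cycle through 0, 2, …, 14. Together they have 198 drinking days and 30 × 14 − 198 = 222 abstinent days.

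- Under-calling: the criterion flags t/2 days. Total 99, sensitivity 99/198 = 0.50, Spearman = 1.00. Mean difference (TAC − TLFB) = −99/30 = −3.3 days.
- Over-calling: the criterion flags 7 + t/2 days. Total 309, false positives 309 − 198 = 111, specificity 1 − 111/222 = 0.50, Spearman = 1.00. Mean difference = +111/30 = +3.7 days.
- Random misses: each drinking day is detected with probability 0.5, with no false positives. In simulation (30 participants, 14 days, three assumed spreads of drinking) median Spearman was 0.81, 0.87 and 0.90. That is high, but not perfect.

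The mean difference shows the bias in the first two cases and Spearman does not.

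**2. Spearman on yes/no days.** Here it equals phi. With drinking-day share p, sensitivity Se, specificity Sp and flagged share q = p·Se + (1 − p)(1 − Sp):

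phi = (Se + Sp − 1) × √[p(1 − p) / (q(1 − q))]

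kappa = (po − pe)/(1 − pe), where po is observed agreement and pe = pq + (1 − p)(1 − q)

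With Se = Sp = 0.90 throughout (po = 0.90):

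| Drinking days p | q | phi | pe | kappa |
|---|---|---|---|---|
| 0.50 | 0.50 | 0.80 | 0.500 | 0.80 |
| 0.10 | 0.18 | 0.62 | 0.756 | 0.59 |
| 0.05 | 0.14 | 0.50 | 0.824 | 0.43 |

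The sensor is the same in every row. The direction depends on the type of error: with Se = 0.50 and Sp = 1, phi is 0.64, 0.58 and 0.48 at p = 0.3, 0.5 and 0.7. Kappa moves with prevalence more than phi does, so it is no remedy for comparing arms.

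**3. Unit.** BACtrack Skyn calls TAS 15, 60 and 90 definitions of a drinking event, then classifies participant-days by them. TLFB classifies calendar days. Only the sensitivity clause in Statistical Analysis counts events. No event-level reference is described.

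**4. Clustering, if intervals are reported.** Sensitivity uses drinking days only. Assuming about 7 per participant (30 × 7 = 210 days), the design effect is 1 + (7 − 1) × ICC:

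- ICC 0.1: 1.6, so 210/1.6 ≈ 131 effective days
- ICC 0.5: 4.0, so 210/4.0 ≈ 53 effective days

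In simulation (true sensitivity 0.80, 14 days, drinking share uniform across participants), a Wilson 95% interval that treats days as independent gave:

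| ICC (assumed) | Coverage | Half-width as computed | Half-width needed |
|---|---|---|---|
| 0.05 | 90% | 0.054 | 0.065 |
| 0.1 | 85% | 0.054 | 0.075 |
| 0.2 | 76% | 0.054 | 0.090 |
| 0.3 | 69% | 0.053 | 0.105 |
| 0.5 | 60% | 0.053 | 0.124 |

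**The case against.** The strongest reply is that Spearman is an added line and not the basis of the accuracy claim. The stated focus is sensitivity, specificity, PPV and NPV, and the criterion that halves everyone's drinking days would show a sensitivity of 0.50 there. The article only says it will explore the criteria; no rule picks one by rho. This stands, and it limits the harm. It does not make Spearman suitable for the one task the article gives it.

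Four stronger readings are tempting, and the article does not support them.

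- A reader might infer that a poor criterion can look perfect under any reading. That holds only for counts, and only when misses are exactly proportional. On yes/no days phi reaches 1 only with perfect agreement.
- A reader might infer that the arms would differ on every accuracy index. For a sensor of fixed performance, sensitivity and specificity do not depend on prevalence.
- A reader might infer that the reported error bars will be too narrow. None is planned in the article, and handling of repeated days may sit in an analysis plan that is not shown. On the count reading each participant contributes one pair, so Spearman itself has no clustering by day. Nor would a design effect of 1 + 13 × ICC on all 420 days (30 × 14) fit sensitivity, which uses drinking days only.
- A reader might infer that PPV mixes units. The article gives no unit for PPV, and the BACtrack Skyn section largely settles the matter on participant-days. What remains is one clause that conflicts with it.

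**Conclusion.** The point holds in a limited form. Spearman is the wrong statistic for comparing the TAC criteria on either reading. On counts it does not register systematic miscounting (rho = 1.00 at sensitivity or specificity of 0.50; about 0.81 to 0.90 with random 50% misses). On yes/no days it depends on prevalence (0.80 to 0.50 for a fixed 0.90/0.90 sensor as drinking days fall from 50% to 5%). The event wording for sensitivity contradicts the day-based definitions in the BACtrack Skyn and TLFB sections and should be reconciled with them.

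The clustering part is conditional: intervals would be too narrow if days were treated as independent, by an amount that rests on an assumed ICC. The prevalence and sensor figures are illustrative. The matter touches a secondary objective of a 30-person feasibility trial, and the planned indices already give much of the protection needed once their unit is fixed. It is worth correcting but does not threaten the trial's main purpose.

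**What to change.** 1. In Statistical Analysis, change the sensitivity clause from alcohol events to alcohol-drinking days, so that sensitivity, specificity, PPV and NPV all come from one participant-day table per criterion.
2. Compare TAS 15, 60 and 90 on day-level sensitivity and specificity. Replace Spearman, or at least supplement it, with the mean difference and limits of agreement of per-participant drinking-day counts (TAC minus TLFB) for each criterion. Keep both parts, because false positives and misses can cancel in a mean difference.
3. Do not rely on day-level kappa or phi to compare arms. Use sensitivity and specificity for that.
4. If intervals are reported for the day-level indices, compute them with participant as the cluster (cluster bootstrap or GEE).

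No new data are needed, and the article reports that analysis is still under way. The cost is a little more analysis code and, where intervals are given, wider ones.
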